#### Secondary objectives

To estimate the impact of glucocorticoids on the incidence of early and intermediate adverse effects of RAI during the first 3 months post therapy (all types, all grades, any duration).To describe comparatively between treatment and control groups the onset, duration, recurrence and severity of early and intermediate adverse effects of RAI during the first 3 months after completion of RAITo evaluate the impact of glucocorticoids on the incidence, severity and type of all adverse effects assessed as related to glucocorticoidsTo evaluate the impact of glucocorticoids on the patient-reported outcomes related to adverse effects of RAI at 2 weeks and 3 months after completion of RAITo study the impact on the quality of life at 2 weeks and 3 months, first overall between treatment groups, then focusing on patients who have experienced a complication of RAI

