### Study assessments

Participants will be given an information sheet and will be explained in detail about the study, and informed written consent will be taken prior to recruitment. The basic demographic information including age, sex, ethnicity and medical history including the details related to thyroid cancer (such as type, grade, stage, lymph node involvement), comorbidities and the current treatment will be collected using the clinic notes and interviewer-administered questionnaire. The contact details will also be collected for the purpose of follow-up. A general physical examination will be performed for a baseline assessment prior to administration of RAI. Basic haematological parameters including full blood count and renal functions will be performed before RAI treatment. A baseline quality of life scores which are EQ-5D-5L and FACT H&N will be measured [10]. Data collection tool is attached in the Supplementary file.

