#### Randomization (or stratification) procedures

At study entry, patients will be randomly allocated to one of the two arms, the intervention arm and the placebo arm. Randomization will be balanced (1:1), using permuted blocks, and stratified according to the total dose of RAI given for stratification into three groups. Criteria for stratification will be 50–100, > 100 and < 200, and > 200 mCi.An independent investigator will be responsible for randomization of treatment using an online randomization software, ensuring concealment of treatment allocation for the next patient.

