### Follow-up procedures

All patients will be given a symptom diary and instructions will be given how to maintain it. Patients will be instructed to bring the diary at each follow-up visit through telephone reminders. If they develop a problematic adverse effect, they will be instructed to contact the investigator. During visit 1 at 2 weeks, clinical interviews will be conducted to assess the adverse effects including oral and eye examination. The adverse effects will be recorded based on the CTCAE grading system by the investigator and also by patient-reported outcome measures NCI PRO-CTCAE. The patients will be reminded about the follow-up visits by phone calls. Data on patients who discontinue the trial or deviate from the protocol will be recorded.

The quality of life instruments including EQ-5D-5L and FACT H&N will be completed by the patient. During visit 2 at 3 months, the same assessment will be conducted with more emphasis on the intermediate adverse effects.

Criteria for removal from protocol therapy include participant requests to be withdrawn from therapy and unacceptable toxicity such as infections, hyperglycaemia or severe dyspepsia. Furthermore, a patient who would prematurely stop the treatment will not be withdrawn from the study unless he/she requests to be withdrawn from the study. There are no specific concomitant treatments or interventions that are permitted or prohibited during the trial.

Off-study criteria include completed 3-month follow-up period, subject withdrawal from the follow-up period and death.

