### Data analysis

#### Sample size calculation

The reported rates of radiation thyroiditis are approximately 20% whilst acute radiation sialadenitis is 12–67% and chronic sialadenitis and xerostomia were 20% [5, 6]. Based on these available data, we assume that clinically significant adverse effects will be reported at 3 months in 20% of patients. At a 2-sided 5% alpha level, a total of 200 patients in each group is required to ensure an 80% power if glucocorticoids are associated with a 10% absolute reduction (10% vs. 20%).

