### Statistical analysis

Analyses will be performed in accordance with the intention-to-treat analysis principle.

All randomized participants randomized to study and control groups will be included in the main analyses irrespective of protocol adherence (i.e. intention-to-treat analysis). An additional per-protocol analysis will also be conducted only including the patients who adhered to the treatment protocol with completed follow-up. For each patient, the maximum grade for all types of events will be calculated over the whole observation period. The maximum grades per patient will be tabulated, first considering all adverse effects, then focusing on clinically relevant adverse effects as defined in Table 1 (primary endpoint). The proportion of patients who have experienced clinically relevant adverse effects will be estimated in each group. Difference of proportions between the 2 treatment groups as well as odds ratio will be provided to estimate the impact of glucocorticoids on the risk of clinically significant RAI therapy-related adverse effects. All these estimates will be provided with their 95% confidence intervals. Analyses will be adjusted on the stratification factors. Comparisons between groups on binary endpoints will be performed using a logistic regression, and comparisons between groups on continuous endpoints will be performed using *t* tests. The *p* value will be evaluated at the 5% level of significance. No adjustment will be made for multiple comparisons associated with secondary analyses, but these will be evaluated in proper context and fully reported.

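### The t tests named for continuous endpoints cannot carry the promised stratum adjustment and give the baseline quality-of-life scores no role; the quality-of-life look in patients with complications should be labelled descriptive

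*Protocol article*

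**What the plan says.** All places are in the protocol article.

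- **Statistical analysis.** "Analyses will be adjusted on the stratification factors". The next sentence gives logistic regression to binary endpoints and states that "comparisons between groups on continuous endpoints will be performed using" t tests.
- **Randomization (or stratification) procedures.** "Randomization will be balanced (1:1), using permuted blocks, and stratified according to the total dose of RAI given". There are three RAI dose strata.
- **Study assessments.** "A baseline quality of life scores which are EQ-5D-5L and FACT H&N will be measured". Baseline evaluation lists the same two instruments before treatment.
- **Follow-up procedures.** "EQ-5D-5L and FACT H&N" are completed again by the patient at 2 weeks and at 3 months.
- **Secondary objectives.** Quality of life at both visits is to be studied "first overall between treatment groups, then focusing on patients who have experienced a complication of RAI".

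No other section names an adjusted model for continuous endpoints, states a use for the baseline scores, or says whether the complication-only look is descriptive or comparative.

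**The concern.** Two adjacent sentences do not fit together for continuous endpoints. Logistic regression can include the dose stratum and a t test cannot. The protocol names the method, so this is not simply a detail left for a later document.

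The same t test makes no stated use of a baseline score measured on every patient. Baseline is usually the strongest available predictor of a follow-up quality-of-life score. What is at stake is precision on EQ-5D-5L and FACT H&N, which bear on the article's stated hope of better quality of life.

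The second quality-of-life look raises a different issue. Reducing complications is the primary objective. If the drug works, the patients with a complication in the two arms are differently selected groups, and a contrast between them loses the protection of randomisation.

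**Working it through.** **The plan's own figure.** The only sample size calculation is for the binary primary endpoint: 20% against 10%, two-sided 5%, 80% power. With the pooled-variance formula,

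n = [1.960 × √(2 × 0.15 × 0.85) + 0.842 × √(0.20 × 0.80 + 0.10 × 0.90)]² / 0.10² = 198.96, so 199 per arm.

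Power at 200 per arm is 80.2%. The stated 200 reproduces and is not in question. No figure is given for a continuous endpoint.

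**Baseline adjustment.** Taken from the plan: 200 per arm and two-sided 5%. Assumed, because the document gives neither: an effect of 0.25 SD and a baseline-to-follow-up correlation ρ of 0.3 to 0.7. No dropout is applied.

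- t test on the follow-up score: SE = √(2/200) = 0.100 SD; power = Φ(0.25/0.100 − 1.960) = 70.5%.
- ANCOVA multiplies the variance by 1 − ρ².
- t test on change from baseline multiplies it by 2(1 − ρ).

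| ρ | ANCOVA variance factor | ANCOVA power | Change-score variance factor | Change-score power | n per arm for ANCOVA to match the plain t test with 200 |
|---|---|---|---|---|---|
| 0.3 | 0.91 | 74.6% | 1.40 | 56.1% | 182 |
| 0.5 | 0.75 | 82.3% | 1.00 | 70.5% | 150 |
| 0.6 | 0.64 | 87.8% | 0.80 | 79.8% | 128 |
| 0.7 | 0.51 | 93.8% | 0.60 | 89.8% | 102 |

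The two factors differ by 2(1 − ρ) − (1 − ρ²) = (1 − ρ)², which is never negative. ANCOVA is therefore never less precise than the change score.

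**Stratum omitted.** Let the strata explain a share R² of the outcome variance (assumed) and let allocation be balanced within strata. The t test then overstates the SE by 1/√(1 − R²), and its true two-sided error is 2[1 − Φ(1.960/√(1 − R²))]. This is 4.4%, 3.9%, 2.8% and 1.9% for R² of 5%, 10%, 20% and 30%. The test is conservative, not anti-conservative.

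**Complication-only look.** Suppose complication means the primary-endpoint event. The planned rates then give 0.10 × 200 = 20 prednisolone and 0.20 × 200 = 40 placebo patients. SE = √(1/20 + 1/40) = 0.274 SD, and the difference detectable with 80% power is (1.960 + 0.842) × 0.274 = 0.77 SD.

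The direction of any bias depends on how the drug acts. Take a standard normal latent severity.

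- *Only the mildest cases are prevented, with no drug effect on quality of life.* Mean severity among cases is 1.400 at 20% and 1.755 at 10%, a gap of 0.355. At correlations of 0.3, 0.5 and 0.7 with quality of life (assumed), prednisolone looks worse by 0.11, 0.18 and 0.25 SD.
- *Same model with a broader definition, 60% against 50% (assumed).* Means are 0.644 and 0.798, a gap of 0.154. The shift is 0.05 and 0.08 SD at correlations of 0.3 and 0.5.
- *Every patient's severity falls by the constant that takes 20% to 10%,* that is 1.282 − 0.842 = 0.440. Mean realised severity among prednisolone cases is 1.755 − 0.440 = 1.315 against 1.400 on placebo. The sign reverses. The gap of 0.085 is also far from the 0.440 by which severity actually fell.

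**The case against.** The strongest reply has four parts.

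1. The adjustment sentence follows the text on the difference of proportions and the odds ratio, so it may govern only the binary analysis. That reading is possible. But the sentence speaks of analyses without restriction, and even on the narrow reading the t test still leaves the baseline scores and the strata unused.
2. The t test might be on change scores, a detail an article can leave to a fuller document. This is fair, so it cannot be stated as fact that baseline is ignored; only that no use of it is stated. It does not rescue the choice, because the change score is never more precise than ANCOVA, and below a correlation of 0.5 it is less precise than the plain follow-up score.
3. The consequence is efficiency on secondary endpoints for which no power is claimed, and the size of the gain rests on assumed values. This stands.
4. The complication-only wording may only set an order of presentation, and no test is stated for it. This stands too. A descriptive reading would be acceptable, but the objective is framed as impact on quality of life and nothing labels this part descriptive.

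A reader might infer that the subset analysis would make an effective drug look harmful. The documents do not support that. The sign changes with the model, the size depends on what counts as a complication, which the objective does not define, and the shifts computed at the planned rates are smaller than one standard error (0.274 SD).

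**Conclusion.** The point holds as a modest one. For continuous endpoints the named test does not fit the promised stratum adjustment, and the collected baseline scores have no stated use. Under the assumed 0.25 SD effect and complete data on 200 per arm, ANCOVA on baseline raises power from 70.5% to between 74.6% and 93.8% for correlations of 0.3 to 0.7. The range, not any single value, is the finding. Omitting the strata makes the t test conservative to the extent that dose predicts the outcome.

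A reader might go further and infer that the t test biases the trial's quality-of-life result, or that the primary analysis is affected. Neither follows. Randomisation protects the overall comparison without adjustment, and logistic regression for the primary endpoint can carry the strata. Nor is the absence of PRO-CTCAE from the listed baseline instruments an error, since comparing randomised arms after treatment is valid without it.

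For the complication-only look, what can be said is that a between-arm contrast would not be protected by randomisation, that its bias has no direction known in advance, and that at the planned rates it would be imprecise.

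**What to change.** 1. In Statistical analysis, replace the t test for the quality-of-life scores by ANCOVA of the 2-week and 3-month score on arm, baseline score and RAI dose stratum as used at randomisation. A mixed model over both visits with the same covariates serves equally. This also brings the test into line with the adjustment sentence.
2. In Secondary objectives, state that quality of life in patients who had a complication will be summarised descriptively by arm, with no between-arm test and no claim of effect.

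The cost is a change of wording. No patients, visits or questionnaires are added, and the sample size and primary analysis stay as they are. Any intention to test the arms within the complication group is given up. Trial status reports that recruitment has not begun, so both changes can be made before any outcome is seen.

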## Discussion

The adverse effects of RAI may be long lasting and may considerably impact the quality of life of patients. The treatment of adverse effects of RAI is mainly symptomatic. This includes proper hydration, use of sialagogues, antiemetics and proton pump inhibitors, and in cases of inflammatory tumour expansion, glucocorticoids may be administered [5, 6]. This is the first randomized control clinical trial designed to assess the effectiveness of prophylactic steroids in reducing the adverse effects of RAI. We hypothesize that a short course of prophylactic prednisolone would be beneficial in reducing the early and intermediate adverse effects of RAI.

Glucocorticoids have significant anti-inflammatory and immunosuppressive properties through its genomic and non-genomic effects [19]. Due to its effect of reducing serum IgG after RAI therapy, this might reflect a decrease of any potential immune-mediated cytotoxicity elicited by the radiation [20]. Furthermore, glucocorticoids may also have a direct radioprotective effect by reducing the intracellular oxidative stress, but it needs further clarification [20]. Also, inflammatory tumour expansion is implicated in the pathogenesis of certain adverse effects such as neck swelling and tracheal compression [6]. Therefore, a short course of glucocorticoids is recommended in patients with symptoms of neck swelling and discomfort following RAI which is seen in large thyroid remnants [6, 21]. Furthermore, glucocorticoid prophylaxis has been recommended in cases where thyroid tumour deposits are suspected near vital structures or in confined anatomical spaces such as the brain, spinal cord, lungs or bone to prevent or minimize the effect of inflammatory tumour expansion [6, 21]. Probable adverse effects of glucocorticoids, such as poorly controlled diabetes mellitus, gastric and duodenal ulcers or electrolyte disorders, should be considered when using glucocorticoids [6]. However, such adverse effects are rare when used for a short duration following exclusion of patients with contraindications for glucocorticoids.

Benefits to subjects will be directly related to the reduction of adverse effects of RAI provided that glucocorticoids are efficacious in reducing such effects. If the glucocorticoids are proven effective, this prophylactic measure could be incorporated to routine practice to minimize adverse effects of RAI. Potential risks would include potential adverse effects of short course of glucocorticoids; however, proton pump inhibitors will be concurrently administered to minimize gastrointestinal adverse effects. Other rare adverse effects include transient increased susceptibility to infections, transient hyperglycaemia, sleep disturbances, altered sensorium and mood changes. In the event of adverse effects to the subjects, medical or professional intervention will be sought. All participants will be educated about the adverse effects of RAI and the safety precautions that should be taken after administration.

If proven to be effective, short-term steroid prophylaxis could be made standard with the administration of RAI treatment for differentiated thyroid cancer which would minimize side effects and improve quality of life.

### Trial status

Recruitment for this trial (version 2.0 on 21 November 2019) has not been commenced yet. The anticipated date for commencement is on 1 November 2020.

## Data Availability

Not applicable, no datasets are included in this study protocol.

## Abbreviations

RAI: Radioactive iodine
ECOG: Eastern Cooperative Oncology Group
HIV: Human immunodeficiency virus
FACT H&N: Functional Assessment of Cancer Therapy Head and Neck
CTCAE: Common Terminology Criteria for Adverse Effects
PRO-CTCAE: Patient-Reported Outcomes-Common Terminology Criteria for Adverse Effects
DSMB: Data and Safety Monitoring Board
